#### Implementation of care

After the study visits have been completed, data extractions from the general practitioners and/or pharmacies will be performed to retrieve data of cardiovascular risk monitoring and changes in cardiometabolic medication prescriptions from 6 months after the SALINE study visit of the participant.

#### **9.4 Withdrawal and replacement of individual subjects**

Subjects can leave the study at any time for any reason if they wish to do so without any consequences. The investigator can decide to withdraw a subject from the study. There are no specific criteria for withdrawal. Every subject that meets the inclusion criteria is invited, therefore replacement is not possible.

#### **9.5 Replacement of individual subjects after withdrawal**

Not applicable

## **9.6 Follow-up of subjects withdrawn from treatment**

Not applicable

## **9.7 Premature termination of the study**

The end of the study is defined as the end of the elaborated screening visit phase. There are no predefined criteria for premature termination of the study. If, however, the investigator/sponsor terminates the study without prior agreement of the subsidizing party, the investigator/sponsor should instantly inform the subsidizing party and provide them with a detailed written explanation for the termination of the study. If the subsidizing party terminates the trial, the subsidizing party should instantly inform the investigator/sponsor with a detailed explanation for the termination of the study.

# **10 SAFETY REPORTING**

## **10.1 Temporary halt for reasons of subject safety**

In accordance with section 10, subsection 4, of the WMO, the sponsor will suspend the study if there is sufficient ground that continuation of the study will jeopardize subject health or safety. The sponsor will notify the accredited METC without undue delay of a temporary halt including the reason for such an action. The study will be suspended pending a further positive decision by the accredited METC. The investigator will take care that all subjects are kept informed.

## **10.2 AEs, SAEs and SUSARs**

### **10.2.1 Adverse events (AEs)**

Adverse events are defined as any undesirable experience occurring to a subject during the study. All adverse events reported spontaneously by the subject or observed by the investigator or his staff during the elaborate screening phase will be recorded.

### **10.2.2 Serious adverse events (SAEs)**

A serious adverse event is any untoward medical occurrence or effect that

- Results in death;
- Is life threatening (at the time of the event);
- Requires hospitalisation or prolongation of existing in subjects' hospitalisation;
- Results in persistent or significant disability or incapacity;

- Any other important medical event that did not result in any of the outcomes listed above due to medical or surgical intervention but could have been based upon appropriate judgement by the investigator.

An elective hospital admission will not be considered as a serious adverse event.

Any SAE that happens during the elaborate screening phase will be reported

The sponsor will report the SAEs through the web portal *ToetsingOnline* to the accredited METC that approved the protocol, within 7 days of first knowledge for SAEs that result in death or are life threatening followed by a period of maximum of 8 days to complete the initial preliminary report. All other SAEs will be reported within a period of maximum 15 days after the sponsor has first knowledge of the serious adverse events.

### **10.2.3 Follow-up of adverse events**

All AEs will be followed until they have abated, or until a stable situation has been reached.

Depending on the event, follow up may require additional tests or medical procedures as indicated, and/or referral to the general physician or a medical specialist.

SAEs need to be reported till end of study within the Netherlands, as defined in the protocol.

## **11 STATISTICAL ANALYSIS**

Characteristics of subjects recruited will be described as mean values with standard deviation or median with interquartile range for continuous variables. Categorical variables will be described as numbers and percentages of the subjects per category.

The overall prevalence of elevated albuminuria, and prevalences of unrecognized and persistent elevated albuminuria despite a RAS-inhibitor are described as percentages with 95% confidence intervals. The number of eligible patients from general practices who fulfilled the inclusion criteria but had an albuminuria level  $<3$  mg/mmol recorded within 18 months prior to selection (and where therefore not invited to participate), will be included in the denominator to calculate the prevalences.

To compare effectiveness and costs of screening on elevated albuminuria in pharmacies and in GP-care, the costs for the targeted screening strategies in both pharmacies and GPs will be calculated.

For each approach, all costs associated with the screening will be added and divided by the total number of subjects identified with confirmed elevated albuminuria. A screening-

approach will be considered more effective than the other if the costs per identified patient are  $\geq 10\%$  lower.

Frequencies of cardiovascular monitoring and treatment changes are summarized as numbers and percentages with 95% confidence intervals.

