asked to collect urine using the PeeSpot and to send this to GPRI by postal mail for a measurement of albuminuria in the laboratory. Subjects will be informed about the results and, only in case of elevated albuminuria levels, the subject will be asked to repeat the procedure for a confirmational measurement. If the confirmational measurement is negative, a third measurement is needed. If recent (<11 months ago) albuminuria levels were available from the general practice and found to be elevated as well, a second confirmational PeeSpot measurement will not be needed. If recent albuminuria levels recorded by the practice were not elevated, subjects will be considered as not having elevated albuminuria and will be included in the calculation of the prevalences but will not be approached to participate. When albuminuria is confirmed, treatment status will be reviewed, and cardiovascular risk factors will be assessed during a visit. Measurements performed during this visit are non-invasive and part of standard care in general practice and therefore not associated with additional risks. A benefit for the subject could be that elevated albuminuria may be detected earlier because of the screening, and thus comes with health benefits, such as adequate treatment of impaired renal function and medication monitoring by the pharmacy, which has been proven to be effective in preventing adverse events of medication.

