#### Targeted screening via general practitioners

General practitioners will select eligible subjects for albuminuria screening from subjects' electronic medical records, based on the presence of risk factors for elevated chronic kidney disease. Using a VIPlive selection report, subjects will be selected based on recording of one or more of the following:

3. An ICPC code for Diabetes Mellitus
4. An ICPC code for cardiovascular disease, including hypertension
5. An ICPC code for lipid disorders
6. An ICPC code for obesity or a calculated BMI  $\geq 30$  kg/m^2, based on height and weight

If albuminuria status was recently (within 18 months) assessed by the general practice and was found to be 'normal' (< 3.0 mg/mmol), subjects will not be invited for albuminuria screening. All other subjects with an increased risk of chronic kidney disease will be invited by their general practice to participate.

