### 5.3 Exclusion criteria

- Inability to understand and sign the informed consent form
- Pregnancy
- Know normal (<3mg/mmol) albuminuria status with 18 months prior

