#### Evaluating non-response:

Aggregated data of characteristics from the total population of subjects that is eligible for screening will be collected from each general practice through VIPLive and will be combined to describe pooled characteristics of the total eligible population from general practices (Table 2).

*Table 2. Distribution of characteristics of the study population selected from participating general practices*

| Characteristic                         | Distribution              |
|----------------------------------------|---------------------------|
| Age                                    | Mean (standard deviation) |
| Sex, female                            | Number (%)                |
| Diabetes Mellitus                      | Number (%)                |
| Elevated albuminuria in last 11 months | Number (%)                |
| Lipid disorder                         | Number (%)                |
| Obesity                                | Number (%)                |
| Hypertension                           | Number (%)                |
| Cardiovascular disease                 | Number (%)                |
| Kidney disease                         | Number (%)                |

Pharmacies will be asked to provide similar data used to select their subjects.

The distribution of subject characteristics in the total selected population will be compared with the distribution among responders using collected information to evaluate occurrence of systematic response bias. Collected information of responders will be used for post-stratification and weighting methods to account for potential response bias in the estimation of prevalences (19).

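### Section 11 adds all never-invited known-normal GP patients to the prevalence denominator without saying that responders are first scaled up to the number invited; read literally, this understates prevalence.

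*Protocol*

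**What the plan says.** Section 11 reports the overall, unrecognized and persistent prevalences, which "are described as percentages with 95% confidence intervals". For the denominator it gives one explicit rule: the count of eligible GP patients with a normal value in the 18 months before selection "will be included in the denominator to calculate the prevalences".

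Section 4.1 (GP route) says of patients with such a value that "subjects will not be invited for albuminuria screening", and section 5.3 lists the same status as an exclusion criterion. The Summary paragraph on burden and risks confirms how they are classified: "subjects will be considered as not having elevated albuminuria and will be included in the calculation of the prevalences but will not be approached".

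Everyone else must respond to be counted. Under section 4.1 a result requires a returned urine sample and consent form, and under section 13.3 the research institute sees no data on invited patients until they return their material. A recent elevated practice value replaces only the confirmatory test (sections 4.1 and 9.3), so that patient must still respond.

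On non-response, section 11 adds: "Collected information of responders will be used for post-stratification and weighting methods to account for potential response bias in the estimation of prevalences". Table 2 lists the characteristics to be collected. Elevated albuminuria in the last 11 months is among them; a known normal value is not.

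**The concern.** The denominator combines two groups observed in different ways. The known normals are a complete count and by definition contain no cases. The invited patients hold every case but are seen only in part. Adding the first group at full size to the responders from the second gives the zero-case group more weight than its share of the eligible population.

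The result then depends on how many people post back a sample and how much testing the practices had already done, as well as on how common albuminuria is. This affects primary endpoint 1, and the same denominator sentence covers the unrecognized and persistent prevalences. A figure that is too low could make targeted screening look less productive than it is. The cost per identified patient does not use this denominator and is unaffected.

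**Working it through.** **Inputs.** The protocol gives no expected prevalence, response rate or known-normal count, so there is no planned figure to reproduce. Its only planning numbers, in section 5.4, are at least 6300 eligible and at least 112 examined at the elaborated visit. Everything else below is assumed and shown as a range.

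**Formula, GP part.** Let I be the number invited, K the known normals, k = K/(I+K), r the response, and p the prevalence among the invited, with response unrelated to albuminuria.

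- Target: I·p/(I+K), taking the protocol's classification of K as non-cases.
- Literal section 11: r·I·p/(r·I+K).
- Ratio of literal to target: r/(k + r(1−k)).

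| r | k=0.2 | k=0.3 | k=0.5 |
|---|---|---|---|
| 0.3 | 0.68 | 0.59 | 0.46 |
| 0.4 | 0.77 | 0.69 | 0.57 |
| 0.6 | 0.88 | 0.83 | 0.75 |
| 1.0 | 1.00 | 1.00 | 1.00 |

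**Is full response likely?** 112/6300 = 1.8%. If prevalence were 10%, response times visit attendance would be 0.018/0.10, about 18%. Both planning figures are minima and attendance is mixed in, so this is only indicative.

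**Worked example, GP part.** Assume 4200 GP-eligible, k=30%, r=40%, and 8% confirmed.

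- Known normals 1260; invited 2940; responders 1176; cases among responders 94.
- Literal: 94/(1260+1176) = 94/2436 = 3.9%.
- Target: 0.70 × 8% = 5.6%. Ratio 0.69.

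**Pooled with pharmacies.** Assume the remaining 6300−4200 = 2100 come from pharmacies, with the same r and the same 8%: 840 responders and 67 cases.

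- Literal: (94+67)/(2436+840) = 161/3276 = 4.9%.
- Target: (235+168)/6300 = 403/6300 = 6.4%. Ratio about 0.77.

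**What the planned weighting could do.** Assume 2000 GP patients with diabetes (k=0.6, p=25%, r=0.4) and 4000 without (k=0.2, p=10%, r=0.25). Invited: 800 and 3200. Known normals: 1200 and 800. Responders: 320 and 800. Target: (200+320)/6000 = 8.7%.

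- No weighting: (80+80)/(1120+2000) = 5.1%.
- Responders weighted by characteristics, weights rescaled to the responder count: 1120 × 13%/3120 = 4.7%, where 13% = 520/4000.
- Responders and known normals pooled, then post-stratified on diabetes: (2000 × 80/1520 + 4000 × 80/1600)/6000 = 5.1%.
- Responders expanded to all eligible, then known normals added: (500+400)/(6000+2000) = 11.3%.
- Responders expanded to the invited total, then known normals added: 520/6000 = 8.7%, the target.

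Only the last form is unbiased, and the protocol does not single it out.

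**Selective response.** The downward bias is cancelled if responder prevalence exceeds invited prevalence by the factor (k + r(1−k))/r. That factor is 1.5 at r=0.4, k=1/3, and 2.3 at r=0.2, k=1/3.

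**The case against.** The strongest reply is that section 11 already commits to post-stratification and weighting. In ordinary survey use that means weighting respondents to population totals, and how the weights are scaled is commonly left to an analysis plan, which is not at hand. Nor does section 11 say that the rest of the denominator is a raw count of responders. This part stands: a reader might infer that the primary prevalence is certain to be biased downward, and the protocol does not support that. The weighting text leaves the correct expansion open, one permitted reading biases upward, and strongly selective response could cancel or reverse the effect.

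A reader might also infer that the handling of known-elevated patients always lowers the estimate. Table 2 lists recent elevated albuminuria, so weighting could correct for under-response in that group.

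The 12–54% understatement implied by ratios of 0.88 to 0.46 applies to the GP part only. The primary endpoint pools both routes, and pharmacy responders dilute it.

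The reply does not dispose of the point. The denominator sentence is a positive instruction in the protocol, and its plain reading gives a wrong result. Table 2 omits known-normal status, the variable on which the chance of being counted differs most.

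The look-back wording is a lesser matter. Sections 4.1, 5.3 and 11 agree on 18 months ("If albuminuria status was recently (within 18 months) assessed by the general practice"). The Summary defines recent as under 11 months when describing elevated values, and then repeats the word for normal ones: "If recent albuminuria levels recorded by the practice were not elevated, subjects will be considered as not having elevated albuminuria". A reader might infer real doubt about who is invited, but the methods sections are consistent.

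**Conclusion.** The concern holds as a badly fixed rule, with a bias that is probable but not certain. Read literally, section 11 understates GP prevalence by the factor r/(k + r(1−k)), and pooled prevalence by less, whenever response is below 100% and responders are not strongly enriched for albuminuria. The GP ratio is 0.46–0.88 for k of 20–50% and r of 30–60%. The pooled ratio is about 0.77 in the example with 2100 pharmacy patients, k=30% and r=40%. These sizes rest on assumed k and r and on response unrelated to albuminuria, so the actual size cannot be determined from the protocol. The stated weighting does not settle it: in the two-stratum example, permitted readings run from 4.7% to 11.3% around a target of 8.7%.

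**What to change.** Replace the denominator sentence in section 11 with a stratified estimator:

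- Weight responders, by recruitment route, so that the weights sum to the number invited (GP) or selected (pharmacy).
- Add the GP known normals as a separate stratum of weight 1 with zero cases: GP prevalence = N_invited × weighted responder prevalence / (N_invited + N_known-normal).
- Combine the two routes using their eligible totals, and take the variance from the responder strata.
- Apply the same approach to the unrecognized and persistent prevalences.
- Record the number invited and the number known normal per practice alongside Table 2, and report the responder-only prevalence as well.

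Separately, reconcile the Summary's look-back wording for normal values with sections 4.1, 5.3 and 11.

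The cost is wording, two counts per practice and a wider interval. In the GP example, with simple binomial variances, the 95% half-width goes from 1.96 × √(0.0386 × 0.9614/2436) = 0.8 points to 0.70 × 1.96 × √(0.08 × 0.92/1176) = 1.1 points. The narrower interval is not real precision, because it surrounds the wrong value.

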### Targeted screening phase

Pharmacies and GPs select potential subjects based on the medical history and last 6 months of prescriptions and registered indications, as described in section 5.2. During this phase subjects will be asked to give written informed consent to participate in the study. Subjects will collect urine samples using the PeeSpot and sent the samples to the laboratory. Furthermore, they receive a questionnaire to collect subject characteristics. The informed consent form and the subject characteristics questionnaire are sent to the General Practitioners Research Institute (GPRI). GPRI will receive the results of the urine tests. If albuminuria is elevated, subjects receive a second PeeSpot to perform a confirmational measurement. If subjects are recruited via GPs and have an elevated albuminuria measurement performed less than 11 months ago, only one extra albuminuria measurement is necessary.

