### **13.3 Storage of personal data**

The handling of personal data will proceed confidentially. The pharmacy and general practitioner are offered the opportunity to use an ISO-certified post order company specialized in security for sending out the invitations. The data of eligible subjects will be handled in the secure and specialized environment of the post order company and will be destroyed after 21 days. Subjects receive a unique study identification number. GPRI has no access to the data of eligible subjects who will be invited. Only when subjects have signed the informed consent and have provided data by returning the completed questionnaire, GPRI receives pseudonymized patient data because the IC and questionnaire are marked by the identification number. During the analysis phase, all data provided by patients that signed the informed consent form are used pseudonymized. The identification number is not linked to the participant's personal information. A subject identification code list will be used to link the data to a participant, the key to the code will be safeguarded by the coordinating investigator. The de-identification process will only be used to contact the participant or his/her general practitioner if they have given consent.

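### Section 11 counts GP patients with a recorded normal result in full but everyone else only if they respond, so the GP part of the prevalence is low unless responders are weighted up to the number invited

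*Protocol*

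**What the plan says.** Three groups of GP patients are treated differently.

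- **Recorded normal.** Section 4.1 does not invite patients with a normal result within 18 months, and section 5.3 lists them as excluded. Section 11 nevertheless says that their number "will be included in the denominator to calculate the prevalences". The Summary (nature and extent of the burden) agrees: such patients are "included in the calculation of the prevalences but will not be approached to participate".
- **Recorded elevated.** These patients are invited. Under section 9.3, if they "have an elevated albuminuria measurement performed less than 11 months ago, only one extra albuminuria measurement is necessary". The record replaces the confirmatory kit, but one PeeSpot must still come back.
- **No usable recent result.** Section 4.1: "All other subjects with an increased risk of chronic kidney disease will be invited by their general practice to participate". Their status is known only through participation.

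Section 13.3 adds that "GPRI has no access to the data of eligible subjects who will be invited".

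Under its non-response heading, section 11 collects aggregate characteristics of the eligible GP population. Table 2 has the row "Elevated albuminuria in last 11 months" but none for a recorded normal result. The same text plans post-stratification and weighting for response bias. It does not give the total to which responders are weighted, or say how the recorded normals join the weighted data.

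**The concern.** Known non-cases enter the denominator at 100%. Everyone who could be a case enters numerator and denominator at the response rate. A percentage built this way falls as response falls, and falls further where practices already test more, even if the true prevalence is unchanged. A larger sample does not shrink the error, and the 95% confidence interval does not reflect it.

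The quantity at stake is primary endpoint 1. Section 11 words the denominator rule for the prevalences in general, so the unrecognized and persistent prevalences are affected too.

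**Working it through.** **Figures in the plan.** The protocol gives no expected prevalence or response rate. Section 5.4 gives at least 112 patients examined out of at least 6,300 eligible: 112/6,300 = 1.8%. Dividing by the Introduction's 5-9% for the general population implies 36% to 20% participation and confirmation combined. Dividing by its 15-25% for hypertension implies 12% to 7%. Both counts are minimums, so this shows only that low response is compatible with the plan.

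**General result.** Let w be the recorded-normal share of at-risk GP patients, r the response among those invited and p the prevalence among those invited. Recorded normals count as non-cases, and response is unrelated to status.

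- Truth: (1-w)p
- Plain percentage: r(1-w)p / [w + r(1-w)]
- Ratio: r / [w + r(1-w)]

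Prevalence cancels. The relative shortfall depends only on r and w, which are both assumptions:

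- w = 15%, r = 60%: 0.60/0.66 = 0.909, a shortfall of 9%
- w = 45%, r = 30%: 0.30/0.615 = 0.488, a shortfall of 51%

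**Illustrative GP case (all inputs assumed).** Take 4,200 GP patients: 30% recorded normal, 3% recorded elevated and 67% without a usable result. Response is 35%. Elevation is confirmed in 75% of the recorded-elevated and 6% of the no-result group.

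- Truth: 0.03 × 0.75 + 0.67 × 0.06 = 6.27%
- Cases counted: 0.35 × 4,200 × 0.0627 = 92
- Denominator: 0.30 × 4,200 + 0.35 × 4,200 × 0.70 = 1,260 + 1,029 = 2,289
- Plain percentage: 92/2,289 = 4.0% (95% CI 3.2 to 4.8), a 36% relative shortfall

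**Pooled with pharmacies.** Let the other 2,100 of the 6,300 be pharmacy subjects with the same response and prevalence. They add 735 responders and 46 cases: 138/3,024 = 4.6%, a shortfall of about 27%.

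**Effect of weighting.** Take an assumed list of 1,000: 300 recorded normal, 50 recorded elevated (80% confirmed) and 650 untested (10% elevated). The truth is (40 + 65)/1,000 = 10.5%. Let 40% of the untested and 50% of the recorded-elevated respond, giving 260 + 25 = 285 responders.

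- Plain: (26 + 20)/(300 + 285) = 7.9%
- Weights that restore the invited mix but sum to 285: 285 × 0.15/585 = 7.3%
- Weights that expand to the 700 invited, plus 300 normals at weight 1: 105/1,000 = 10.5%
- Recorded normals left out: 105/700 = 15.0%, too high for the whole at-risk group

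If responders are expanded to a total that already contains the recorded normals, and these are then added again, the ratio to the truth is 1/(1-w²). At w = 30% that is 1/0.91, about 10% too high.

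**The case against.** The strongest reply is that section 11 itself plans post-stratification and weighting, and nowhere makes an unweighted percentage the reported primary result. A reader might infer from the denominator rule that the reported prevalence will be biased low. The document does not support that. Weights that expand responders to all those invited would remove the bias, provided response is random within cells. Weight construction is also commonly left to a statistical analysis plan, which is not at hand.

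Much of this stands, but it does not settle the point. The denominator rule is fixed in the protocol, while the weighting text is aimed at differences in characteristics between responders and the selected population. Weights of that kind leave the shortfall almost intact (7.3% against 10.5% above). The target total is unclear as well: section 5.3 excludes known-normal patients, whereas section 11 calls them eligible.

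Three further limits stand:

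- **Direction is not guaranteed, even unweighted.** The bias cancels if prevalence in responders is 1 - w + w/r times that in all invited. At w = 30% this is 1.20, 1.45 or 2.20 times for r = 60%, 40% or 20%. The protocol has no data on this.
- **Section 11 specifies an overall prevalence.** The GP-route figures therefore overstate the effect on it.
- **The count of recorded normals is already required by section 11.** Only its use is open.

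A reader might also infer that recorded normals should not be in the denominator. That is not so: leaving them out biases the estimate upward.

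**Conclusion.** The concern holds in limited form and should be fixed. The stated denominator rule, used as a plain percentage or with weights that only rebalance responders, makes the GP contribution too low unless response is complete or cases respond much more often than non-cases. With response unrelated to status, the GP-route shortfall is about 9% to 51% over w of 15-45% and r of 30-60%. It is smaller for the overall prevalence: about 27% instead of 36% in the illustrative case if a third of the 6,300 come from pharmacies. All these sizes rest on assumed inputs. Whether the final estimate is biased depends on a weighting choice that the protocol does not state.

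**What to change.** In section 11, state the following:

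1. GP prevalence is estimated by prior-test stratum: recorded normal, recorded elevated within 11 months, no valid result. Responders in each invited stratum are weighted to the full number invited, and recorded normals are counted once at weight 1. With full counts N and confirmed fractions c among responders, the estimate is (N_elevated × c_elevated + N_none × c_none) / (N_normal + N_elevated + N_none).
2. The confidence interval uses the stratified variance.
3. The overall prevalence combines this with pharmacy responders weighted to the number invited there.
4. The unrecognized and persistent prevalences use the same denominator.
5. Table 2 shows the recorded-normal count beside the elevated row.

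The windows also need reconciling. The Summary ties a recent result to 11 months and then says of those not elevated that "subjects will be considered as not having elevated albuminuria and will be included in the calculation of the prevalences but will not be approached". Sections 4.1, 5.3 and 11 use 18 months for a normal result. The window sets the size of the recorded-normal group.

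The cost is small. Only aggregate counts are needed for non-responders, which is compatible with section 13.3, and responders' recorded-elevated status is already needed to decide on one kit or two. The interval widens somewhat. In the illustrative GP case the two invited strata have about 44 and 985 responders, so the standard error is √(0.03² × 0.1875/44.1 + 0.67² × 0.0564/984.9) = 0.54 percentage points. The interval is then about 5.2% to 7.3% around 6.27%, ignoring clustering by practice. The estimate still relies on response being random within strata.
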